Participants of both groups will attend for 2–8 treatment sessions over 4 weeks. The exact number of treatments needed to achieve an optimal change is not presently known, so a range allows the practitioner to exercise their clinical judgement. We have chosen two as the minimum number of treatments, because usual clinical practice would involve a minimum of two visits to enable re-assessment following the initial treatment [39]. The actual number of treatment sessions delivered to participants in each group will be determined according to the clinical judgement of the treating practitioner, who is a registered physiotherapist with a post-professional tertiary qualification in the field of manual therapy and more than 20 years of clinical experience in treating musculoskeletal conditions. The physiotherapist will also be individually instructed in the MWM intervention by an accredited member of the Mulligan Concept Teachers Association. The physiotherapist will conclude the course of intervention if the patient reports they have fully recovered or if no further improvement is possible up to a limit of eight sessions over a 4 week period. The number of sessions and the duration of each session will be recorded. The same measures taken at baseline will be repeated at the conclusion of the course of intervention, within a maximum of 4 days after the participant’s last intervention session. Further measurements will be repeated at the twelfth week with the exception of the imaging, and only self-report outcomes will be assessed at 12 months. Participants will be contacted by telephone every 4 weeks after finishing treatment for up to 1 year to record any new ankle injuries, any treatments undertaken, and their level of engagement in sport and other activities. Figure 1 describes the flow of the study.

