## Sample size and data analysis

Previously published data related to the primary outcome measure of function (FAAM subscales, ADL and sports) [18, 34] (MCID = 8.0, SD = 5.68; MCID = 9.0, SD = 7.42 respectively) were used in sample size calculations [18, 34, 72]. A sample size of 16 per group allowing for a 30% drop-out rate was estimated, for a minimal statistical power of 0.80 and an alpha significance level of 0.05. Secondary analysis based on the subgroups of ankle instability (mechanical, functional) will be preliminary in nature as the study is not powered for this aim.

Data will be analysed using SPSS Statistics for Windows (Version 23.0, Armonk, NY, IBM Corp). Continuous data will be assessed for normality using the Shapiro-Wilk test.

Baseline comparability between groups will be analysed using the independent t-test or non-parametric equivalent, as appropriate. Linear mixed models will be used to analyse the outcome measures. For the primary outcome measure, ‘function’ will be the outcome variable and time, group and an interaction term for time by group will be the predictors. Any statistically significant difference in change in the outcome variable over time between the groups will be indicated by the *p* value for the interaction term. Pairwise Bonferroni comparisons will be performed to explore the differences between time points and between groups if a significant interaction is identified. Independent t-tests will be used to compare outcome measures between groups at each time point and the changes of the scores will be used to detect any changes in the outcomes of interest. Intention to treat analysis will be performed with all participants allocated to each group condition to evaluate the effect of the independent variable. For missing data in ITT analysis, a participant’s last observation for each outcome measure will be carried forward. The average number and the average duration of intervention sessions between groups will be compared. If any significant difference observed, secondary analysis will be taken to find any correlation between the treatment volume and the outcomes.

Additional variables recorded during monthly phone interviews (new injuries, changes in activity level, and occurrence of other treatments) will be used as covariates in the analysis of the 12 month follow-up data as they are possible confounders. Further, the Beighton score for hypermobility will also be included in regression analysis as a covariate.

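### Last observation carried forward is fixed as the missing-data rule beside a mixed model that does not need it; it can bias the effect either way and prejudges the 12-month durability question

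*Protocol article*

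**What the plan says.** All the relevant statements are in the protocol article, mostly under Sample size and data analysis.

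- Model: "Linear mixed models will be used to analyse the outcome measures". For the primary outcome, function, "time, group and an interaction term for time by group will be the predictors", and the interaction p value is the test of a difference between groups in change over time.
- Analysis set: "Intention to treat analysis will be performed with all participants allocated to each group condition".
- Missing data in that analysis: the participant's "last observation for each outcome measure will be carried forward".
- Size: "A sample size of 16 per group allowing for a 30% drop-out rate was estimated". The target is 80% power at alpha 0.05, and the FAAM ADL and sport inputs are given as "MCID = 8.0, SD = 5.68; MCID = 9.0, SD = 7.42 respectively".
- Schedule (Procedure): baseline, end of intervention, week 12 and month 12, where "only self-report outcomes will be assessed at 12 months". FAAM function is self-reported, so the primary outcome runs to month 12.

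The aims at the end of the Background include lasting benefit at 12 months. The article gives no reason for carrying observations forward, and nothing elsewhere in it qualifies the rule.

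**The concern.** The two choices work against each other. A mixed model estimated by likelihood keeps every randomised participant who has at least one observation and borrows from that person's earlier visits. Intention to treat therefore does not call for filling the gaps. Filling them first discards this property. A participant lost before the post-treatment visit is recorded as having exactly zero change. One lost after week 12 is given the week-12 score as the 12-month score. The model then counts these values as real measurements, so its variance and degrees of freedom do not reflect what is missing.

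The stake is greatest at 12 months. The trial asks whether benefit lasts, and for everyone lost after week 12 the rule supplies the answer that nothing has changed since.

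**Working it through.** **Inputs from the protocol:** FAAM sport difference 9.0, SD 7.42; FAAM ADL difference 8.0, SD 5.68; power 0.80; alpha 0.05; 30% drop-out allowance; 16 per group.

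**Assumptions, not in the protocol:** two-sided test; timing of loss; outcome trajectories; common improvement in both arms of 0 to 6 points; correlation 0.5 between visits. The power and error rates come from simulating a t-test on two-visit change scores with 16 per arm. That is a stand-in for the planned interaction test. With correlation 0.5 the SD of change is 7.42 × √(2 × 0.5) = 7.42.

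**1. The plan's sample size.** n = 2 × (1.96 + 0.84)² × SD²/difference².
- Sport: 15.7 × (7.42/9.0)² = 10.7, so 11; 11/0.7 = 15.7, so 16. This matches the stated figure.
- ADL: 15.7 × (5.68/8.0)² = 7.9, so 8; 8/0.7 = 11.4, so 12.

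At 30% loss about 5 of 16 per arm (0.3 × 16 = 4.8) would carry a filled value at the last visit.

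**2. Expected difference under the rule.** In each arm, mean = (1 − d) × true mean + d × mean at the last observed visit, where d is the proportion lost. Loss is taken as unrelated to outcome.

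| Scenario | Calculation | Estimate | Truth |
|---|---|---|---|
| 30% lost before any post-treatment visit, effect 9 sustained | 0.7 × 9 + 0.3 × 0 | 6.3 | 9 |
| 30% lost later, effect fades from 9 to 4.5 | 0.7 × 4.5 + 0.3 × 9 | 5.85 | 4.5 |
| 30% lost later, effect fades from 9 to 0 | 0.7 × 0 + 0.3 × 9 | 2.7 | 0 |
| 30% lost later, effect 9 sustained | 0.7 × 9 + 0.3 × 9 | 9 | 9 |

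With equal loss the bias therefore runs from −2.7 through 0 to +2.7 points, against a 9-point minimal important difference.

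**3. Power when all 30% is lost early.** Zero-filling pulls the estimate down and, if participants otherwise improve, adds variance of d(1 − d) × mean² within each arm.
- Common improvement 6: MWM variance 0.7 × 55.06 + 0.21 × 15² = 85.8; placebo 38.5 + 0.21 × 6² = 46.1. Estimate over standard error = 6.3/√(131.9/16) = 2.19. Simulated power 56%.
- Common improvement 0: variances 38.5 + 0.21 × 9² = 55.6 and 38.5. Ratio = 6.3/√(94.1/16) = 2.60. Simulated power 73%.
- Observed data only, about 11.2 per arm: 9/(7.42 × √(2/11.2)) = 2.87. Simulated power 77%, estimate 9.0.

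**4. False positives (simulated).**
- Effect gone by month 12, 30% lost after the earlier visit: about 15% under the rule, about 5% on observed data.
- No effect, 30% early loss in both arms: about 5%, with or without common improvement.
- No effect, early loss 20% MWM and 40% placebo, common improvement 6: bias 0.8 × 6 − 0.6 × 6 = +1.2 points; error about 8%.
- The same unequal loss without common improvement: about 5%.

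**The case against.** The strongest case for leaving the rule alone is that the harm is conditional, and much of this stands.

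- The 30% is an allowance in the sample size. A reader might take it as the expected loss at a particular visit, but the protocol does not say that. Putting all of it before the first post-treatment visit is a worst case, since that visit falls within 4 days of the last session of a course of at most 4 weeks. With 10% early loss the estimate is 0.9 × 9 = 8.1.
- A reader might infer that the rule always biases the effect. It does not: a sustained effect with later loss unrelated to outcome gives none.
- A reader might infer a general inflation of type I error because filled values count as data. With equal early loss the error stays near 5%. The 8% needs both unequal loss and a common improvement, and the protocol predicts neither. Participants are blinded, and the placebo is described as having a strong effect.
- Most of the fall in power to 56% comes from the assumed 6-point common improvement.
- The simulated rates do not transfer exactly to the planned time-by-group test.
- The absence of a sensitivity analysis is not a defect here, since that may be left to an analysis plan that is not shown.

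What does not stand is a defence that the rule is safe or conservative. Its direction depends on timing and balance of loss that cannot be known in advance, and its harmless case assumes the durability that the trial sets out to test. Nor is it a detail deferred to another document, because the protocol fixes it for every outcome.

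**Conclusion.** The concern holds in a conditional form. The protocol adds an unnecessary and stronger assumption to a model that already handles missing visits under missing at random. If the full 30% allowance were lost equally, the difference in FAAM sport could be out by up to 2.7 points in either direction, or by nothing. Power under wholly early loss would be 56% to 73% instead of 77%, for a common improvement of 6 to 0 points. These figures rest on the assumed timing, trajectories and correlation, and they illustrate the risk without forecasting it. The documents do not support a claim that the result will be biased, or that the type I error is inflated in general. The firm part is the 12-month analysis: carrying the week-12 score forward can report as lasting a benefit that has gone.

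**What to change.** Delete last observation carried forward as the missing-data rule for the intention-to-treat analysis. State instead that the mixed model will be fitted by REML to all observed data from all randomised participants, analysed as randomised, without imputation. If last observation carried forward is kept at all, label it as a supplementary analysis. A sensitivity analysis that departs from missing at random would be useful, because the observed-data model rests on an assumption that cannot be verified, but it is optional.

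The cost is a change of wording in the analysis section. The sample size, visits and data collection stay as they are, and the change should be made before outcome data are examined.

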A positional fault at the inferior tibio-fibular joint, is one arthrokinematic abnormality proposed to be related to persistent/recurrent symptoms and repetitive ankle sprains in CAI [4]. In the case of an ankle joint sprain, Mulligan suggests that the distal fibula is ‘mal-positioned’ anteriorly (anterior positional fault) following an inversion injury and that chronicity may result if this remains uncorrected [22, 26]. Preliminary evidence for such an anterior fibular positional fault was identified in Hubbard et al’s study of individuals with CAI [27]. However it is unclear whether ankle instability caused the anterior fibular position or whether the fault itself was actually the predisposing factor to re-injury. Also, the clinical importance of an anterior fibular positional fault in relation to other potential contributors to CAI remains unclear. Further, the mechanism(s) of changes in CAI outcomes after MWM needs to be further investigated [15, 28]. It has been proposed by Mulligan in his positional fault hypothesis, that MWM effects an immediate and lasting improvement by correcting a minor bony incongruity which is the source of the patient’s presenting problem [22]. However, the capacity of MWM to reverse any positional fault remains unclear and further studies are required to assess the effectiveness of this technique.

The objective of this study is to determine the effect of MWM on anatomical and clinical characteristics of CAI, and to determine the long term effectiveness of this treatment.

The specific aims of the study are therefore:To evaluate the effectiveness of MWM on clinically relevant outcomes, including patient-reported outcomes (dorsiflexion range, pain intensity, self- reported function, pressure pain threshold, static and dynamic balance), including long lasting benefits assessed at 12 months post treatment.To assess the effect of MWM on changing the fibular position relative to the position of the tibia in CAI.

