Consenting participants will be randomised into two groups: an experimental group who will receive MWM, and a control group who will receive a placebo (detuned laser). All of the participants will be assessed for general joint hypermobility using the Beighton score [36]. Mechanical ankle instability will be tested separately for each ankle using an X-ray while undergoing an anterior drawer stress test [37, 38]. The clinically important outcome measures will include; radiological imaging of fibular position with respect to the tibia (positional fault), dorsiflexion range of motion (DFROM), pressure pain threshold (PPT), pain intensity, function, static balance and dynamic balance. These procedures and outcome measures are further explained below. The researcher who collects the clinical measurements, and the radiographer taking the X-rays, will be blinded to the participant’s group (intervention) allocation. This researcher will remain blinded to the group allocation until the 3 month follow-up. The 12 month follow-up data will be collected using online questionnaires.

Each participant will be randomly allocated to a group to receive either MWM (active) treatment or detuned laser treatment (placebo) (these interventions are fully explained below). The participant will be blinded as to whether they are receiving an active or placebo intervention, however due to the nature of the interventions, the treating practitioner cannot be blinded. Participants will be randomly allocated to groups according to a computer generated (GraphPad Software, Inc., CA, USA) randomisation schedule by another researcher not involved in data collection using sealed opaque envelopes. Each envelope will contain a piece of paper printed with either ‘1’ or ‘0’, for which ‘1’ denotes ‘MWM’ group and ‘0’ denotes ‘placebo’ group. The treating practitioner will open the envelope and allocate the participant to a group according to the number in the envelope, and deliver the designated treatment accordingly.

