### Other measures

Telephone interviews will be conducted monthly after enrolment up to 1 year to record any new injuries, any treatments undertaken, and the level of engagement in sports and other activities. These variables will be used as covariates in the analysis of the 12 month follow-up data as they are possible confounders. Further, the Beighton score for hypermobility and radiographic measurement of the anterior drawer stress test will be recorded.

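### The 12-month analysis adjusts for new injuries, other treatments and activity level, which arise after randomisation; this is liable to bias the long-term intention-to-treat effect

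*Protocol article*

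**What the plan says.** The rule appears twice. Under Other measures, after describing the telephone interviews, the protocol article states: "These variables will be used as covariates in the analysis of the 12 month follow-up data as they are possible confounders". Under Sample size and data analysis it names new injuries, changes in activity level and other treatments, and again says they "will be used as covariates in the analysis of the 12 month follow-up data as they are possible confounders".

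The timing of the data is given in two slightly different ways. Under Procedure: "Participants will be contacted by telephone every 4 weeks after finishing treatment for up to 1 year to record any new ankle injuries". Under Other measures: "Telephone interviews will be conducted monthly after enrolment up to 1 year to record any new injuries". On either schedule the information comes after allocation ("Consenting participants will be randomised into two groups").

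The long-term question is a stated aim. The Background section sets out to evaluate effectiveness on clinical outcomes, "including long lasting benefits assessed at 12 months post treatment". The analysis section promises intention to treat with all allocated participants.

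The same section describes two analyses without these covariates: a linear mixed model for function with time, group and their interaction as predictors, and independent t-tests between groups at each time point. It does not say which 12-month result answers the long-term aim. It calls the mechanical/functional instability subgroup analysis preliminary, but puts no such label on the 12-month analysis with covariates.

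**The concern.** A confounder of the treatment comparison must influence who receives which treatment. Allocation here is random and precedes every telephone call, so nothing recorded in those calls can play that part. The reason given for the adjustment is therefore wrong.

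The three variables may instead be consequences of treatment, and the Background section supplies the grounds. It defines chronic ankle instability by repeated sprains, so a new ankle injury is a manifestation of the condition. It links the fibular positional fault that MWM is meant to correct to repetitive sprains. It reports less giving way and more confidence in the ankle after MWM with taping, which could change activity. Seeking other care may plausibly follow a poor response.

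If treatment does change these variables, a model that holds them fixed no longer estimates the total effect of being allocated to MWM. Benefit that runs through fewer injuries is taken out of the estimate. Where unmeasured severity drives both injury and function, conditioning on injury also introduces an association between arm and severity that randomisation had removed. What is at stake is the answer to the 12-month question on the primary outcome measure.

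**Working it through.** **Inputs from the protocol article (Sample size and data analysis).** FAAM-sport minimal clinically important difference 9.0, SD 7.42; FAAM-ADL 8.0, SD 5.68; 16 per group with 30% drop-out, power 0.80, alpha 0.05 (two-sided assumed).

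**The plan's own figure.** With n = 2(1.96 + 0.842)² × (SD/difference)²:
- FAAM-sport: 2 × 7.85 × (7.42/9.0)² = 10.7, so 11; 11/0.7 = 15.7, so 16 per group.
- FAAM-ADL: 2 × 7.85 × (5.68/8.0)² = 7.9, so 8; 8/0.7 = 11.4, so 12 per group.

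The stated 16 is reproduced. It is not affected by this point.

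**Assumed inputs.** The document gives no injury rates and no cost of an injury in FAAM points. Assume a true total effect of 9.0 FAAM-sport points at 12 months, new-injury risk p0 = 40% on placebo, p1 = 40%, 30%, 20% or 10% on MWM, and a loss of b = 5, 10 or 15 points per injury.

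**Formula.** Let Y = d × arm − b × injury + error. The total effect is T = d + b(p0 − p1). A model that includes injury estimates d, so

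adjusted estimate = T − b(p0 − p1).

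Example: p1 = 20%, b = 10 gives 9.0 − 10 × 0.20 = 7.0.

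| Injury, placebo v MWM | b = 5 | b = 10 | b = 15 |
|---|---|---|---|
| 40% v 40% | 9.0 | 9.0 | 9.0 |
| 40% v 30% | 8.5 | 8.0 | 7.5 |
| 40% v 20% | 8.0 | 7.0 | 6.0 |
| 40% v 10% | 7.5 | 6.0 | 4.5 |

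A simulation with 1,000,000 participants per scenario agrees with these values to rounding. Without the covariate it returned 8.97 to 9.03 in every scenario.

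**Adding an unmeasured common cause.** Suppose a standard normal severity variable raises injury liability (probit coefficient 0.8) and lowers FAAM-sport by 4 points per SD. The simulated adjusted estimates for b = 5, 10 and 15 become:
- 40% v 30%: 8.1, 7.6, 7.1
- 40% v 20%: 7.2, 6.2, 5.2
- 40% v 10%: 6.2, 4.7, 3.2

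With 40% v 40% the estimate stays at 9.0.

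**Direction.** These cases all understate benefit because injury is the covariate and MWM is assumed to reduce it. The other two covariates can act differently. If more placebo participants obtain effective care elsewhere, the unadjusted difference narrows and adjustment could widen it. Greater activity under MWM could raise exposure to injury. No single sign follows for the three together.

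**The case against.** The strongest reply is that an unadjusted 12-month comparison is already planned: the primary-outcome mixed model carries no such covariates, t-tests are listed at each time point, and the analysis is by intention to treat. This stands as a limit on the point. A reader might infer that the trial will have no intention-to-treat estimate at 12 months, and the document does not support that. What remains is that the covariate analysis is the one written specifically for the 12-month data, it is not labelled exploratory, and no result is named as the answer to the long-term aim.

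A second reply is that participants are asked to avoid concurrent interventions, so other treatment is a departure from the protocol that one may wish to account for. The wish is reasonable. But an effect free of co-intervention is a different target from intention to treat. The document does not state it, and simple covariate adjustment would recover it only if no unmeasured factor drives both the covariate and the outcome.

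Three further inferences go too far:
- **That the 12-month estimate is biased as a fact.** If allocation leaves these variables unchanged there is no bias, and the Background section itself calls long-term benefit of MWM unclear.
- **That a real benefit would be adjusted to nothing.** That requires the whole effect to run through the covariates, for which the document gives no basis.
- **That the model would be fitted to about 22 people** (32 × 0.7 = 22.4). The plan carries the last observation forward for each outcome measure, so outcomes exist for all 32. That rule does not mention the telephone variables, so some participants might still be lost from the adjusted model, but no number can be given.

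**Conclusion.** The point holds as a stated analysis choice with a wrong justification. The three telephone variables arise after randomisation, cannot confound the comparison, and may be changed by treatment on the protocol's own reasoning. An analysis that conditions on them is liable to miss the intention-to-treat effect at 12 months.

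The size is conditional. On the assumed inputs, a halving of injury from 40% to 20% turns a true 9.0 points into 8.0 to 6.0, and equal injury risk gives no bias. These inputs are illustrative; neither the amount nor the sign can be derived from the document. The Beighton score is recorded at the first visit and is not part of the criticism.

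**What to change.** In Sample size and data analysis, and in the matching sentence under Other measures:

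1. Remove new injuries, other treatments and activity level from the main 12-month efficacy analysis, and delete the statement that they are possible confounders.
2. Name the intention-to-treat between-group contrast at 12 months, without post-randomisation covariates, as the main long-term result. Baseline covariates such as the Beighton score may stay.
3. Report new injuries, other treatments and activity level by arm.
4. Label any model that conditions on them as exploratory.

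The cost is analysis wording only. The data to be collected and the 16 per group do not change.

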#### Anterior drawer stress test with radiographic measurement

Ankle joint mechanical instability will be assessed using a lateral x-ray to measure the amount of anterior translation of the talus during a ligament stress test for each ankle. The radiograph will be taken while the ankle is undergoing a simulated anterior drawer test using 125 N force [38]. The stress radiograph will be taken with the participant in a supine lying position with the foot relaxed in a resting position and the lower leg resting on a support, with the hip and knee each flexed approximately 45 degrees. The heel will be supported on a dynamometer (Lafayette Manual Muscle Tester, Model 01165, Lafayette, IN, USA) attached to a customised device which produces the anteriorly directed force. The distal tibia will be fixed on the support using a stabilising belt placed over the distal aspect of the tibia [58]. The central ray will be centred just above the tip of the lateral malleolus and perpendicular to the image receptor [59]. Then an anterior force of 125 N will be applied [38] to the heel of the participant at an angle of 20 degrees to the vertical plane as per recommended clinical practice [60], using the customised device. The force will be monitored using the digital display of the dynamometer attached to the customised device, and the radiograph will be taken at 125 N. The ankle radiograph will be taken at the focal-film distance of 110 cm [61] and will set to 55 kVp and 2.1 mAs. The same procedure will be applied to the other ankle. These images will be taken at the baseline data collection session to assess mechanical instability for use in subgroup analysis.

Radiographic images will be digitally obtained using Merge PACS™ software (Merge Health Care, 2012). Anterior translation of the talus will be measured between the posterior lip of the tibial articular surface and the nearest point of the talar dome (Fig. 3) [61–64] to identify any mechanical instability. Anterior drawer stress radiographs have been found to have moderate sensitivity, high specificity and a high positive predictive value for the evaluation of lateral ankle instability [37]. A between-limb difference of 3 mm in anterior translation of the talus or an absolute value of 10 mm is considered clinically significant [37].

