Radiographic measurement of the anterior drawer stress test will be used to differentiate subgroups of CAI in potential sub group analysis.

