## Discussion

One proposed anatomical mechanism underpinning MWM is theorised to be a correction of a minor bony incongruity (positional fault) which is at the source of the patient’s presenting problem [22, 73]. The existence of an anterior fibular ‘positional fault’ in individuals with CAI has some preliminary radiological support [27]. There are also limited MRI data supporting Mulligan’s positional fault hypothesis in cases of lateral ankle pain [72], however there is no evidence to date that MWM reverses any positional anomaly. Further, should any fibular positional anomaly be reversed immediately after the application of MWM, the length of time this reversal or correction is maintained is unknown. The proposed study protocol is designed to determine the presence of any positional fault of the fibula in CAI, and whether MWM can reverse this, and if so, whether this reversal is evident 4 weeks after treatment commences. Moreover, this study protocol will explore the correlation between an anatomical measure (fibular position) and other clinical outcomes (pain, function, pressure pain threshold, DFROM, static and dynamic balance). Potential relationships between these measures may help explain how changing an anatomical measure may effect a clinically meaningful outcome. The effect of MWM in CAI will also be explored in relation to the presence or not of radiologically measurable mechanical instability.

There are very few clinical trials with long term follow-ups which have assessed MWM for any musculoskeletal condition, and only one for CAI which had a 6 month follow-up [6, 15]. The proposed study protocol is therefore the first designed to evaluate the long term effectiveness of MWM on CAI. Moreover, the treatment effect may depend on the type of instability present (mechanical or functional), and this study protocol may evaluate the efficacy of MWM on these two subgroups of CAI. However, the subgroup analysis will be exploratory as the study was only powered to detect the main effect being the intervention on the functional outcome.

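### A negative stress film cannot be read as functional instability: the exploratory subgroup split leans toward no difference, and talar translation is better analysed in millimetres

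*Protocol article*

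**What the plan says.** Under *Sample size and data analysis*, the protocol article plans a secondary analysis by type of ankle instability, mechanical or functional, and assigns the type by film: "Radiographic measurement of the anterior drawer stress test will be used to differentiate subgroups of CAI in potential sub group analysis". It says that this analysis "will be preliminary in nature as the study is not powered for this aim".

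The section on the anterior drawer stress test says that both ankles are filmed at baseline "to assess mechanical instability for use in subgroup analysis". Talar translation is read in millimetres. Two statements there matter:

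- On the threshold: "A between-limb difference of 3 mm in anterior translation of the talus or an absolute value of 10 mm is considered clinically significant". No other threshold appears in the article.
- On accuracy: the films have "moderate sensitivity, high specificity and a high positive predictive value for the evaluation of lateral ankle instability". No figures are given.

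The Discussion uses two descriptions of the same analysis. One speaks of the effect of treatment "in relation to the presence or not of radiologically measurable mechanical instability". The other returns to two types of instability, mechanical or functional, and adds that "the subgroup analysis will be exploratory as the study was only powered to detect the main effect".

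**The concern.** A test with moderate sensitivity misses some of the ankles it is meant to find. In a two-class split, those ankles fall into the negative class, which the article calls functional. High specificity protects the positive class and does nothing for the negative one. The subgroup comparison then sets a fairly clean group against a mixed one, and a real difference in treatment effect between the two types would look smaller than it is. This is a bias, so the caveat about power does not cover it and a larger sample would not remove it.

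Any cut also discards the millimetre values on either side of it. Those values are collected in every participant, on both ankles, and subgroup analysis is the only analytic use the article states for them. What is at stake is how the exploratory result is read: a finding of no difference by instability type could be taken as evidence that type does not matter.

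**Working it through.** **The plan's own figure.** The sample size rests on FAAM differences of 8.0 (SD 5.68, ADL) and 9.0 (SD 7.42, sport), power 0.80 and alpha 0.05 (taken as two-sided). With n per group = 2(1.96 + 0.84)²(SD/difference)²:

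- Sport: 10.7, so 11; 11/0.70 = 15.7, so 16 per group, as stated.
- ADL: 7.9, so 8; 8/0.70 = 11.4, so 12.

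The stated 16 per group reproduces, and nothing below changes it.

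**Attenuation formula.** Let the true treatment effects be δM (mechanical) and δF (functional).

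- Film-positive group: PPV·δM + (1 − PPV)·δF
- Film-negative group: (1 − NPV)·δM + NPV·δF
- Difference: (PPV + NPV − 1)(δM − δF)

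The factor PPV + NPV − 1 is the share of the true contrast that remains. The share of film-negative ankles that are mechanically unstable is 1 − NPV. This assumes non-differential error: missed mechanical ankles respond to treatment as detected ones do, and likewise for false positives.

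**Inputs.** The article gives no sensitivity, specificity or prevalence. The values here are assumptions: sensitivity 0.5 to 0.7 for *moderate*, specificity 0.95 for *high*, true mechanical share 0.3 and 0.5.

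**One case in full.** Sensitivity 0.6, specificity 0.95, share 0.5:

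- PPV = 0.300/(0.300 + 0.025) = 0.923
- NPV = 0.475/(0.475 + 0.200) = 0.704, so 1 − NPV = 0.296
- Factor = 0.923 + 0.704 − 1 = 0.627, a loss of 37%

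| Share | Sensitivity | PPV | Unstable among film-negative | Factor | Loss |
|---|---|---|---|---|---|
| 0.3 | 0.5 | 0.811 | 18% | 0.627 | 37% |
| 0.3 | 0.6 | 0.837 | 15% | 0.684 | 32% |
| 0.3 | 0.7 | 0.857 | 12% | 0.738 | 26% |
| 0.5 | 0.5 | 0.909 | 34% | 0.564 | 44% |
| 0.5 | 0.6 | 0.923 | 30% | 0.627 | 37% |
| 0.5 | 0.7 | 0.933 | 24% | 0.693 | 31% |

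**Sensitivity to the assumptions.**

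- With perfect specificity the factor equals the NPV: 0.67 at sensitivity 0.5 and share 0.5, and 0.89 at sensitivity 0.7 and share 0.3.
- With specificity 0.90 and sensitivity 0.5 the factor is 0.49 (share 0.3, PPV 0.68) or 0.48 (share 0.5, PPV 0.83).
- Over sensitivity 0.5 to 0.8, specificity 0.90 to 1.0 and share 0.2 to 0.8, the loss runs from 5% to 74%.

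**Power of the contrast without misclassification.** Assume all 32 participants fall in four equal cells of 8. The standard error of the interaction is SD·√(4/8): 4.0 points (ADL) and 5.2 (sport). The difference detectable at 80% power is 2.80 times that, 11.3 and 14.7 points, above the 8 and 9 used for sample size. Power for an interaction of 8 or 9 points is about 51% and 40%. Multiplying the contrast by 0.564 to 0.738 reduces this to about 20–31% (ADL) and 16–24% (sport). Unequal cells would lower these further.

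**The case against.** - **The analysis is optional and disclosed as exploratory.** This stands. It is described as potential, preliminary and unpowered, and an inconclusive result is likely from sample size alone. The caveat, however, concerns precision and not bias toward no difference.
- **The accuracy statement must be read whole.** This also stands. A reader might infer that the functional group contains many unstable ankles and that up to half the contrast is lost. The article supports neither. A loss of half needs sensitivity near 0.5 with specificity near 0.90, or a high mechanical share. If high PPV means at least 0.90, the cases that remain at specificity 0.95 are those with share 0.5, giving 31% to 44%. Half is not an upper bound either, as the wider grid shows.
- **The split rule is inferred.** The analysis section does not repeat the 3 mm and 10 mm thresholds, and the accuracy statement is not tied to the either-or rule, which would generally be more sensitive than either criterion alone. This is fair. They remain the only thresholds given, in the section that introduces the films for subgroup analysis.
- **The Discussion once words the question as radiologically measurable instability.** On that wording, a film-negative ankle is correctly classified by definition. The difficulty arises where the article moves to mechanical versus functional types, as it does in the analysis section and again in the Discussion.
- **Continuous or cut is a modelling choice often left to an analysis plan.** True, and published thresholds are not an error. What the article does fix is the classifying test and the name functional for the negatives.

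**Conclusion.** The point holds as a minor one. On the article's own description of the test, the film-negative group will include some mechanically unstable ankles and should not be called functional. Given non-differential misclassification, the subgroup contrast is biased toward no difference. The direction follows from the text; the size does not. Under the assumed sensitivity of 0.5 to 0.7, specificity of 0.95 and mechanical share of 0.3 to 0.5, the loss is roughly 26% to 44%, with 12% to 34% of film-negative ankles mechanically unstable.

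A reader might go further and infer that the trial's main conclusion or its sample size is compromised. The documents do not support that: the primary comparison does not use the film, and the 16 per group reproduces.

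**What to change.** - In the exploratory FAAM model, enter baseline talar translation of the affected ankle in mm as a continuous modifier: translation plus group-by-translation. In the planned mixed model the treatment effect is read from time-by-group, so translation must be carried into that interaction.
- Report the estimated group difference with 95% CI across the observed range of translation.
- Repeat with the between-limb difference in mm as a sensitivity analysis.
- Keep the 3 mm/10 mm split as a descriptive display. Label its groups radiographic mechanical instability *present* and *not detected*, in line with the Discussion's radiological wording, and state that a negative film is not evidence of functional instability.

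The cost is analysis wording only, with no new data and no change to the primary analysis. There are three downsides. The modification is assumed linear. With about 32 participants a few extreme translations may have leverage. Measurement error in the film itself remains and will still dilute the interaction to some degree.
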